### Primary outcome

The first primary effectiveness outcome will be VO_2peak_ using a modified Bruce protocol on the cycle ergometer. Briefly, peak oxygen consumption (VO_2peak_) will be determined using an incremental graded cycle ergometer test. The person will properly seated and the bicycle adjusted for optimally positioning. Rate of Perceived Exertion (RPE), heart rate, and blood pressure will be taken at each workload, in addition to assessing oxygen consumption and CO_2_ production. The person will cycle for 3 minutes at 0 watts, 10 watts and 20 watts (9 minutes) and subsequently, at intervals of 1 minute, the work load will be increased by 10 watts. People will be considered to have reached their peak exertion if one of the following criteria are met [80]: (i) reached their age-predicted heart rate of 220-age; (ii) a rating of perceived exertion of at least 17 on the Borg scale; (iii) a respiratory rate of 35 breaths per minute; (iv) pedalling rate of 50 to 80 repetitions per minute cannot be maintained; or (v) the person says they can do no more. Our effectiveness indicator is the proportion of people making a 10% change in VO_2peak_ at the end of the 12 month intervention.

In addition, each person will also complete, the Modified Canadian Aerobic Fitness Test (mCAFT) [81], which is a graded step test and can predict VO_2peak_ using the regression equation we have recently published [46]. This test will be completed only at interim evaluations (3, 6, and 18 months) or if the person misses one of the VO_2peak_ assessments.

### Secondary outomes

A second primary effectiveness outcome will be a global test based on creating binary response variables for all relevant outcomes using known clinically meaningful change to indicate response (or ½ SD if this is not known [82]) (see Table 1).

Adherence and exercise engagement will be monitored using a combination of exercise diaries and accelerometers. The exercise diaries are a good short-term method and also serve as a way for the participants to track their progress as well as any symptom changes (positive or negative) such as fatigue or pain. We will use daily diaries for the first 3 months and subsequently ask people to complete a diary and wear an accelerometer for one of the weeks in the month preceding their scheduled assessment. The weeks for the diary and for the accelerometer will not coincide.

### Sample size

Sample size is based on a test of proportions. Assuming a range of response proportions in the General Guideline Group of 0.2 to 0.5, we have powered this study at 80% to detect a relative risk of >1.5 in favour of the MSTEP Group (Type I error 0.05). A sample size of 120 per group (total sample size of 240) is targeted.

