**Methods/Design:**

The proposed study is an assessor-blind, parallel-group, randomized controlled trial (RCT). The duration of the intervention will be one year with follow-up to year two. The targeted outcomes are exercise capacity, functional ambulation, strength, and components of quality of life including frequency and intensity of fatigue symptoms, mood, global physical function, health perception, and objective measures of activity level. Logistic regression will be used to test the main hypothesis related to the superiority of the MSTEP program based on a greater proportion of people making a clinically relevant gain in exercise capacity at 1 year and at 2 years, using an intention-to-treat approach. Sample size will be 240 (120 per group).

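### With 120 per group, 80% power for a relative risk of 1.5 is reached only from a control response of about 0.36, not across the stated 0.2 to 0.5

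*Protocol article*

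**What the plan says.** The Sample size section bases the calculation on a comparison of two proportions. The control response is given as a range, with one power for all of it: "Assuming a range of response proportions in the General Guideline Group of 0.2 to 0.5, we have powered this study at 80" per cent. The effect is likewise stated once: the aim is to "detect a relative risk of >1.5 in favour of the MSTEP Group", with "Type I error 0.05". The result is one number: "A sample size of 120 per group (total sample size of 240) is targeted". The abstract repeats the 240, and Trial design gives 1:1 allocation.

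Under Primary outcome, the endpoint being powered is the proportion of people with a 10% change in VO2peak at 12 months. The section does not say whether the test is one- or two-sided. It names no single planning rate within the range and mentions no allowance for loss.

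**The concern.** With a fixed relative risk, the absolute difference grows with the control rate. A relative risk of 1.5 is a difference of 0.10 at a control rate of 0.20 and of 0.25 at 0.50. One sample size therefore cannot give the same power at both ends. If 120 per group gives 80% somewhere inside the range, it must give less below that point.

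This is the article's only power statement, and it concerns the confirmatory comparison. No rate within the range is preferred, so 0.20 is as much a planning assumption as 0.50. If few control participants gain 10%, the trial has much less chance of detecting its target effect than readers are told. A null result would then be over-read as evidence against MSTEP.

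**Working it through.** **Inputs.** From Sample size: control response p0 from 0.20 to 0.50, relative risk 1.5 (the boundary of the stated effect), alpha 0.05, power 80%, n = 120 per group. From Trial design: 1:1 allocation. Two-sided testing is assumed, because sidedness is not stated; one-sided is shown alongside.

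**Formulas** (pooled-variance normal approximation), with p1 = 1.5·p0, p̄ = (p0 + p1)/2 and Δ = p1 − p0:

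- n per group = [1.960·√(2p̄(1−p̄)) + 0.842·√(p0(1−p0) + p1(1−p1))]² / Δ²
- power = Φ{ [Δ·√n − 1.960·√(2p̄(1−p̄))] / √(p0(1−p0) + p1(1−p1)) }

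**Attempt to reproduce the plan's figure at p0 = 0.20.** Here p1 = 0.30, p̄ = 0.25 and Δ = 0.10.

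- √(2·0.25·0.75) = 0.6124; √(0.16 + 0.21) = 0.6083
- n = (1.960·0.6124 + 0.842·0.6083)² / 0.01 = 293.2, so 294 per group
- power at 120 = Φ[(0.10·10.954 − 1.2002)/0.6083] = Φ(−0.172) = 43%

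**At p0 = 0.36.** Here p1 = 0.54, and the same formulas give n = 119 and power 80.4%. The 80% line is crossed at p0 = 0.358. The failing part of the range is therefore (0.358 − 0.20)/(0.50 − 0.20) = 53%.

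| Control | MSTEP at RR 1.5 | n per group for 80%, two-sided | Power at 120, two-sided | Power at 120, one-sided 0.05 | RR detectable with 80%, two-sided |
|---|---|---|---|---|---|
| 0.20 | 0.300 | 294 | 43% | 56% | 1.81 |
| 0.25 | 0.375 | 215 | 55% | 67% | 1.68 |
| 0.30 | 0.450 | 163 | 67% | 78% | 1.58 |
| 0.35 | 0.525 | 125 | 78% | 87% | 1.51 |
| 0.40 | 0.600 | 97 | 88% | 93% | 1.45 |
| 0.50 | 0.750 | 58 | 98% | 99% | 1.35 |

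**Other ways to obtain the stated figure (two-sided unless noted).**

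- Exact binomial power of the Pearson test: 43.4% at 0.20 and 79.8% at 0.36.
- Unpooled variance, log relative risk and log odds ratio (the logistic-regression scale): 43.7%, 42.3% and 42.8% at 0.20. Each reaches 80% between about 0.35 and 0.37.
- Continuity correction: 80% is reached at 0.376.
- One-sided 0.05: 231 per group needed at 0.20; 80% is reached at about 0.31.
- Reading 240 as the size of each group, contrary to the text: still only 72% at 0.20.

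None gives 80% over the whole range.

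**Loss to follow-up (assumption; the article gives no figure).** If 20% had no usable 12-month value and contributed nothing, 96 per group would remain. Power at 0.20 would then be 36%, and 80% would be reached only from about 0.40. With 10% loss the figures are 40% and about 0.38.

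**The case against.** The strongest counter-argument is the inequality sign. The plan says "detect a relative risk of >1.5 in favour of the MSTEP Group", not exactly 1.5. The detectable relative risks at control rates of 0.20 to 0.35 are 1.81 to 1.51, all above 1.5, so on a loose reading the sentence is vague rather than false. At 0.35, the middle of the range, the detectable value is 1.51, so the trial may have been sized there. But the ordinary reading of the sentence is 80% power for relative risks from 1.5 upward throughout the range. That fails: at 0.20, a relative risk of 1.6 has 56% power and 1.7 has 69%. The loose reading survives only if the target is an unstated value as high as 1.81.

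Sidedness also matters. The hypothesis is directional, and under a one-sided 0.05 test the failing part shrinks to (0.312 − 0.20)/0.30, or 37% of the range. Power at 0.20 is then a little above one half. This reduces the shortfall without removing it.

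Three further points stand:

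- Even two-sided, power below 50% occurs only near the bottom of the range, and nothing in the article shows that the control rate will lie there.
- The loss figures are illustrative. The plan substitutes predicted VO2peak from submaximal tests and uses multiple imputation, so the complete-case calculation is not a forecast, and an allowance may be given in the full protocol.
- The article deliberately chooses a binary outcome for interpretability, so a continuous analysis can only be an addition.

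**Conclusion.** The stated power is wrong as written. For a relative risk of 1.5, 120 per group gives 80% or more only from a control response of about 0.36. Power falls to 43% at 0.20, where nearly two and a half times the planned number would be needed (294 against 120). These figures assume a two-sided 0.05 test and a usable 12-month result from all 240 people. With a one-sided test the corresponding figures are about 0.31 and 56%. The design is adequate for a relative risk of 1.5 in the upper part of the range. The conclusion rests only on inputs printed in the Sample size section and does not depend on any assumed loss.

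**What to change.** Restate the Sample size section, including the sidedness. Suggested wording, if the test is two-sided:

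> With 120 per group, a two-sided 0.05 test has 80% power for a relative risk of 1.5 if the general-guideline response is at least 0.36. At responses of 0.20, 0.25 and 0.30 the relative risk detectable with 80% power is 1.81, 1.68 and 1.58. These figures are before loss to follow-up.

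This costs a few lines and a less favourable stated power. It needs no extra patients and leaves the primary analysis unchanged.

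A separate, optional addition is to pre-specify a baseline-adjusted between-group comparison of log VO2peak at 12 months as the first supportive analysis, keeping the responder proportion primary. Suppose individual change is normal with equal spread in both groups, which the article does not establish. The standardised shift is then d = Φ⁻¹(p1) − Φ⁻¹(p0), and power is Φ(d·√(120/2) − 1.960). For 0.20 against 0.30, d = −0.524 + 0.842 = 0.317, and power is Φ(0.497) = 69%. The shifts that give 43%, 55% and 67% power on the responder scale give about 69%, 79% and 87% on the continuous scale. The cost is one extra model.

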### Randomization

Randomization will be stratified by site, Montreal and Toronto and persons will be randomly assigned, within their strata, either to the MSTEP or General Guidelines using blocked randomization. The block sizes will be 2, 4 and 6 and the size of the block will also be randomly assigned. The randomization will be done using web based program < <http://www.randomization.com.> > by a statistician who will be the only person with access to the code. When the outcome assessments have been completed by the assessment staff, the statistician will reveal the group assignment to the intervention staff.

Since funding was secured for this trial, there has been increasing interest in prescribing Fampyra to increase gait speed and thus an additional strata was created to avoid having an imbalance of people on Fampyra (dalfampridine;prolonged-release fampridine tablets) in one of the groups [83,84].

### Blinding

It is not possible to blind the participants as to their group assignment. Participants were informed that we were comparing two exercise programs and one was not presented as potentially superior to the other, protecting against bias in responses to the self-report outcomes.

Evaluators will be blinded. The main outcome is based on an assessment of VO_2peak_ which has standard procedures for administration to ensure that the subject puts as much effort as possible into the test. The test is done off-site using existing personnel who may or may not be the same for each subject or each assessment within subject. It is not a test that is strongly affected by unblinding of the testing staff. Nevertheless, the testing staff will not be informed of the group assignment. The situation for the other assessments is similar as they are performance based tests. These will be done by an assessment team of students who will vary over time but also will not be told of the group assignment.

During the analysis, the code for the group assignment is not revealed until all analyses are completed and validated.

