### Outcomes

The targeted outcomes are exercise capacity, exercise efficiency, functional ambulation, strength, and components of quality of life including frequency and intensity of fatigue symptoms, mood, global physical function, health perception, and illness intrusiveness. Also collected will be exercise adherence, exercise enjoyment, socio-demographic, adverse events, and clinical information including relapse rate. The complete portfolio of outcomes [55-79] is listed in Table 1.

**Table 1 T1:** Outcomes for MSTEP Study

**Construct**	**Measure**	**Clinically relevant change**
Primary Outcome		
Exercise capacity	V0_2peak_	10% change[32,55,56]
Components of Global Outcome		
Exercise efficiency: Gross, net and work efficiency	Gross efficiency = work performed / energy expended × 100%, Net efficiency = work performed / energy expended above rest × 100%, and Work efficiency = work performed / energy expended above that in cycling at 0 W × 100% [57].	10% change [58].
Sub-maximal exercise capacity	The Modified Canadian Aerobic Fitness Test (mCAFT) is a multi-stage step-test, simple to use and inexpensive, that assesses sub-maximal aerobic capacity [59].	1 stage [59]
Functional ambulation	Modified 6 Minute Walk Test (M-6MWT) [60]; distance and fatigability index calculated by [the distance walked in the last minute ÷ distance walked in the first minute], with ratio ≥ 1.0 indicating less fatigability; Reliability high (ICC across 3 walks, 0.95).	50 m. [32,60-64].
Strength	Grip, vertical jump, push-ups, curl-ups [65]	½ SD: jump 5cm; curl ups 5; push ups 3; grip strength 12 [46].
Fatigue symptoms	Unidimensional Fatigue Impact Scale [66]; which is a Rasch validated measure of fatigue modeled from the original and modified versions [60,67]	Minimum clinically important difference(MCID) 5; ½ SD = 6 [66].
Mood*	Rand-36 MHI subscale [68,69];	Meaningful change: 10
Global physical function*	Rand-36 PF subscale [68,69]	Meaningful change = 10
Health perception*	EQ-5D [70-73]	Meaningful change = 10
Quality of life*	Patient Generated Index* [74,75]	Meaningful change ½ SD = 12.5
Explanatory Variables		
Current disability level	PDDS (patient version of EDSS) for all persons [76]	
Relapses	Defined as “patient-reported or objectively observed events typical of an acute inflammatory demyelinating event in the CNS, current or historical, with duration of at least 24 hours, in the absence of fever or infection.” [47]; annualized rate over study period	

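### Five of the nine constructs in the global outcome are self-reports by unblinded participants, so a reporting difference alone could open the gate to the separate outcomes; the analysis should show performance and self-report components separately

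*Protocol article*

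**What the plan says.** Protocol article, Blinding. The first paragraph concedes that "It is not possible to blind the participants as to their group assignment". It then says participants were told that two programmes were being compared and that "one was not presented as potentially superior to the other, protecting against bias in responses to the self-report outcomes". The second paragraph turns to evaluators. It describes VO2peak testing by staff who are not told the arm, and continues: "The situation for the other assessments is similar as they are performance based tests". These other assessments are to be done by students who are also not told the arm.

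Protocol article, Outcomes. The targeted outcomes include "components of quality of life including frequency and intensity of fatigue symptoms, mood, global physical function, health perception, and illness intrusiveness". Under the Table 1 heading "Components of Global Outcome" there are nine constructs.

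Protocol article, secondary outcomes section: "A second primary effectiveness outcome will be a global test based on creating binary response variables for all relevant outcomes".

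Protocol article, Statistical methods. Each outcome becomes a binary response, and GEE compares response rates between arms. Separate outcomes may be read as genuine effects only if this test is significant. The text does not distinguish performance components from self-reported ones.

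**The concern.** Keeping the arm from testing staff protects a measurement that staff make. It does nothing for a questionnaire, where the participant is the assessor and knows the arm. For those components the plan relies on neutral presentation alone, and states it as though it were sufficient. Neutral presentation governs what participants are told at entry, not what they experience over a year. Goal setting, planning by mental imagery, a personalised schedule and practice on equipment are described only for MSTEP.

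What is at stake is the meaning of a positive global test. One pooled test mixes components that staff assess without knowing the arm with components that unblinded participants report, and it decides whether the separate outcomes may be interpreted at all. A difference confined to the questionnaires could pass that test, and the result could then be presented as a general benefit in a trial described as assessor-blind.

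**Working it through.** **Step 1: count the components in Table 1.**

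| Construct | Type | Listed measures |
|---|---|---|
| "Exercise efficiency: Gross, net and work efficiency" | performance | 3 |
| Step test (mCAFT) | performance | 1 |
| Modified 6-minute walk (distance, fatigability index) | performance | 2 |
| Strength (grip, jump, push-ups, curl-ups) | performance | 4 |
| Fatigue scale | self-report | 1 |
| Rand-36 mental health | self-report | 1 |
| Rand-36 physical function | self-report | 1 |
| EQ-5D | self-report | 1 |
| Patient Generated Index | self-report | 1 |

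By construct, self-reports are 5 of 9 (56%). By listed measure they are 5 of 3 + 1 + 2 + 4 + 5 = 15 (33%). The article does not say which way components enter. The walk's fatigability index has no change threshold, so fifteen is approximate. Illness intrusiveness is named in the text but is not in Table 1, so it is not counted.

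**Step 2: inputs.** From the Sample size section: 120 per arm. The plan gives no error rate or power for the global test, so there is no stated figure to reproduce. Assumptions: response proportion p = 0.30 on every component, exchangeable latent-normal correlation 0.2, no true effect on anything, and a reporting shift b added to the five self-reports in the MSTEP arm only. A positive test means z > 1.96 in favour of MSTEP, which has a nominal rate of 2.5%.

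**Step 3: hand approximation.** With a common group effect and equal weights, the GEE test behaves much like a comparison of each person's mean response over K components.

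- A latent correlation of 0.2 at p = 0.30 gives a binary correlation φ of about 0.119.
- Variance of a person's mean: p(1−p)/K × [1 + (K−1)φ].
- K = 9: 0.21/9 × (1 + 8 × 0.119) = 0.0455. SE of the arm difference = √(2 × 0.0455/120) = 0.0275.
- A shift b = 0.10 on five of nine moves the mean by 5 × 0.10/9 = 0.0556. Ratio to SE = 2.02. Chance of a positive test ≈ Φ(2.02 − 1.96) = 0.52.
- K = 15: 0.21/15 × (1 + 14 × 0.119) = 0.0373. SE = 0.0249. Shift = 5 × 0.10/15 = 0.0333. Ratio = 1.34. Chance ≈ Φ(1.34 − 1.96) = 0.27.

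**Step 4: simulation under the same assumptions.**

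| Assumed shift on self-reports | 9 components | 15 components |
|---|---|---|
| 5 points | 16% | 10% |
| 10 points | 49% | 26% |
| 15 points | 83% | 51% |

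The hand figures for 10 points (52% and 27%) agree; they run slightly high because they ignore the larger variance in the shifted arm. With no shift the rate is about 2–3%.

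**Step 5: sensitivity.** With response proportions of 0.2 to 0.5 and correlations of 0.2 to 0.4, shifts of 5, 10 and 15 points give 11–24%, 32–64% and 62–91% with nine components. With fifteen they give about 6–12%, 15–34% and 30–63%.

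**Step 6: test possible remedies (nine components, correlation 0.2).** Requiring only that the performance-set estimate lie in the direction of MSTEP lowers 16%, 49% and 83% to 16%, 38% and 48%. That is weak protection, because with no true effect the direction is favourable about half the time. Requiring the performance set to be significant in its own right holds the false functional claim near 2 to 3%, whatever the shift.

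**The case against.** A reader might infer that the authors overlooked the self-report outcomes, or described them as performance tests. The text does not support that. The paragraph before names the self-report outcomes and gives a safeguard. The sentence at issue stands in the paragraph on evaluators and is most naturally read as covering tests given by staff. It is loosely worded, not an oversight.

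The arms are also less unequal than their names suggest. The control programme uses MS-specific guidelines, and both arms get two private sessions, discussion of modifications for MS, a portfolio and the same contact schedule. This makes a large reporting difference less likely but does not exclude one.

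The separate outcomes are to be interpreted after a significant global test, so a reader could often see which components moved. That stands in part: the information would be recoverable. But the plan lets the pooled test alone license the interpretation, and it fixes no rule for a result confined to the questionnaires.

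The status of the global test is mixed. It is called a second primary outcome under a secondary heading, a secondary analysis in Statistical methods, and the hypothesis about multiple outcomes is exploratory in Objectives. The confirmatory VO2peak claim does not depend on it.

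Finally, walking, push-ups and curl-ups depend on the effort of unblinded participants, so the performance set is not perfectly blinded either. That stands and limits what any split can deliver.

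**Conclusion.** The point holds in a limited form. The sentence about performance-based tests is too broad as written. Neutral presentation is the only protection for five of nine constructs (5 of about 15 if every listed measure enters separately), and the pooled GEE that opens the separate outcomes does not distinguish them. A questionnaire-only difference could therefore open that gate.

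How often depends on a bias whose size the documents do not give. At assumed shifts of 5, 10 and 15 points, with 30% response and correlation 0.2, it is about 16%, 49% and 83% with nine components and 10%, 26% and 51% with fifteen, against a nominal 2.5%. These are conditional rates and do not predict that bias will occur.

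A reader might go further and infer that a positive global test would be uninterpretable or that the trial's main conclusion is at risk. Neither follows: component results can be shown, and VO2peak is unaffected.

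**What to change.** 1. In Blinding, limit the sentence to staff-administered tests, and say that neutral presentation may not remove reporting bias from the questionnaires.
2. Keep the pooled GEE as planned. Also fit it separately for the performance and self-report components, and report both estimates with confidence intervals.
3. Base any claim of functional benefit from the global outcome on the performance-set confidence interval excluding no effect. Direction alone is not enough, as the remedy check shows.
4. Label a result seen only in the self-report set as an unblinded patient-reported difference.
5. State whether components enter by construct or by listed measure, since this sets the weight of the self-reports.

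The cost is analysis wording and an extra GEE fit on data already to be collected. The downside is a narrower claim if the true benefit is only patient-reported. The split does not remove the effect of unblinded participants' effort on the performance tests, and the report should say so.
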